### Experimental setup

2.2

In short, the present experiment will comprise four main phases (schematic representation in Figure 2): (1) acquisition of MRI data in awake participants during rest and auditory stimulation, (2) gradual sedation with propofol (~45 min), (3) training session of sedated participants for ~20 min (see below for an explanation) and (4) acquisition of MRI data in sedated participants during rest and auditory stimulation, both repeated twice. During the awake phase a structural (T1) image will be collected prior to the acquisition of functional scans during rest (~10 min) and auditory stimulation (~15 min; for a detailed description of the auditory paradigm, see the section “fMRI experimental design and auditory paradigm”). To prevent the comparison of connected and disconnected consciousness from being contaminated by correlates of (un)responsiveness we will ensure that participants were unresponsive prior to the start of the experimental sessions and awakening. We will also assess their state of wakefulness before and after the experimental sessions to minimise the risk of arousals and confounding correlates of wakefulness with those of (dis)connected consciousness.

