### Variables of interest, randomization, and blinding

2.7

In this experiment, the dependent variable will be the BOLD signal (during RS/task sessions). The independent variables will be both the connected/disconnected condition and the type of sounds delivered, i.e., standard or deviant events or silence. The connected/disconnected condition cannot be randomized, given its unpredictability, i.e., it is impossible to predict which individuals will report being connected and which will report being disconnected. In contrast, several parameters of the auditory paradigm will be randomized (e.g., the number of repetitions of standard events). Similarly, the temporal order of the waking and sedation sessions cannot be randomized given the use of anesthetics: data acquisition after the end of sedation would in fact correspond more to acquiring data during the recovery than during the awakening phase. Finally, the order of the RS and task sessions will not be randomized due to time constraints: since the collection of reports must occur immediately after the task session, if the task preceded the RS session, we would be forced to collect reports after the task and then wait for the participants to lose responsiveness again to acquire the 10 min of rs-fMRI, considerably extending acquisition time. Data preprocessing and analysis will be performed blind to the conditions of the experiment.

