### Preprocessing and statistical analysis

2.9

As we will use a mixed block/event-related design, all the following analyses (see Table 1 for a summary) will be conducted on the BOLD time-series at both the block and trial level: for the block-level analyses, we will contrast (1) task blocks (i.e., standard and deviant blocks combined) with silence blocks and (2) standard vs. deviant blocks. For the trial-level analysis, we will contrast (1) combined deviant and standard trials with BOLD extracted time-series of simulated time points during silence blocks and (2) deviant vs. standard trials. For the purpose of this project and the hypotheses presented, the analysis of RS data will not be discussed in this study.

**Table 1 tab1:** Hypotheses tested and corresponding analyses. This table provides a comprehensive overview of the analyses, brain areas, atlas employed, and statistical methods used for each hypothesis tested in this study.

Hypotheses tested	Analyses	Considered brain areas	Atlas	Statistical analysis
*Hypothesis 1*	Activation analysis (ROI-based)	All 7 sub-thalamic regions (L/R)	Oxford thalamic connectivity atlas	Small volume correction
*Hypothesis 2*	Activation analysis (ROI-based)	Primary auditory cortex (L/R): Heschl’s gyrus	Harvard-Oxford cortical and subcortical structural atlases	Small volume correction
*Hypothesis 3*	Activation analysis (ROI-based)	Secondary regions (L/R): superior temporal gyrus (both anterior and posterior division)	Harvard-Oxford cortical and subcortical structural atlases	Small volume correction
*Hypothesis 4*	ROI-to-ROI based connectivity	2 sub-thalamic (sensory and temporal) nuclei and Heschl’s gyrus	Oxford thalamic connectivity atlas/ Harvard-Oxford cortical and subcortical structural atlases	Subject-level: wGLM Group-level: LME
*Hypothesis 5*	ROI-to-ROI based connectivity	Heschl’s gyrus and superior temporal gyrus (both anterior and posterior division)	Harvard-Oxford cortical and subcortical structural atlases	Subject-level: wGLM Group-level: LME
*Hypothesis 6*	Voxel-to-voxel connectivity	Whole cortical and subcortical brain matters	No atlas	Subject-level: Intrinsic connective analysis Group-level: LME

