#### Group-level analysis

2.9.5

For group-level activation analysis (block/trial) we will perform a linear mixed effect model with nested random effects of subjects within the two experimental sessions, using package lme4 in software R. Fixed effects will be included to control for condition (CC vs. DC), stimulus/block type (deviant vs. standard or silence vs. sound), interaction between stimulus/block type and condition, propofol concentration and time to ROR. The latter allows the investigation of the effect of extending reports back in time, i.e., it is more probable that the subject was in a CC/DC state shortly before awakening as opposed to a long time before awakening. For the group-level connectivity analysis the same procedure will be followed, considering the connectivity matrices or intrinsic connectivity maps as dependent variables.

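### The pre-sedation awake auditory run enters no analysis in the article; as a covariate it could sharpen the part of the CC-DC comparison that is between people, by an amount the article does not let us fix

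*Protocol article*

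**What the plan says.** Section 2.2 (Experimental setup) makes the first phase "acquisition of MRI data in awake participants during rest and auditory stimulation". It adds: "During the awake phase a structural (T1) image will be collected prior to the acquisition of functional scans during rest (~10 min) and auditory stimulation". The auditory run lasts about 15 minutes, and the text refers to section 2.4 for the paradigm, the same description that governs the sedated runs.

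Section 2.9.5 (Group-level analysis) lists the model terms: "Fixed effects will be included to control for condition (CC vs. DC), stimulus/block type (deviant vs. standard or silence vs. sound"), then "interaction between stimulus/block type and condition, propofol concentration and time to ROR". The random effects are "nested random effects of subjects within the two experimental sessions". For connectivity, "For the group-level connectivity analysis the same procedure will be followed".

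Section 2.7 states: "The independent variables will be both the connected/disconnected condition and the type of sounds delivered". It also says that the connected or disconnected state cannot be randomised because it cannot be predicted. Section 2.9 sets one data set aside: "the analysis of RS data will not be discussed in this study". It does not say the same of the awake auditory run.

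**The concern.** The outcome of interest is measured in each participant before sedation, and so before the CC or DC state can occur. The model already adjusts for named covariates, yet this one is absent.

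That matters because CC and DC are not assigned. Some of the comparison will be between different people:

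- Nothing in the design makes a participant connected in one session and disconnected in the other.
- Section 2.3 discards sessions without recall and excludes participants who say they were awake.
- Section 2.2 allows for participants who cannot be aroused, and ends the experiment if a second loss of responsiveness is not reached.

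Wherever the contrast is between people, stable differences in auditory BOLD response or connectivity add noise. If they are associated with who becomes disconnected, they also bias the contrast. The awake value of the same region or region pair measures those differences directly and cannot be a consequence of the state.

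**Working it through.** **1. Is the awake run used anywhere in the article?** I looked for it in each analysis section.

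| Place | Terms or data used | Awake auditory run |
|---|---|---|
| 2.9, block and trial contrasts | task v silence, standard v deviant | no |
| Table 1 | regions, atlas and method per hypothesis | no |
| 2.9.2, first-level model | movement, outlier volumes, elapsed time | no |
| 2.9.3 and 2.9.4, connectivity | ROI pairs, intrinsic connectivity maps | no |
| 2.9.5, group model | condition, stimulus/block type, interaction, propofol concentration, time to ROR | no |
| 2.9.6, spectral analysis | CC v DC | no |

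**2. The plan's own sample size.** Inputs from section 2.8: two-sided t-test, alpha 0.05, power 0.95, d = 0.85, equal allocation. With 37 v 37 sessions the noncentrality is 0.85 × √(37 × 37 / 74) = 3.66 on 72 degrees of freedom, which gives power 0.950. The stated 74 sessions reproduce.

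**3. Gain if sessions are independent, as section 2.8 treats them.** Let r be the correlation between the awake and the sedated value of the same outcome. The article does not give it, so a range is assumed. Adjustment multiplies the residual variance by 1 − r², so d becomes d / √(1 − r²).

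| r (assumed) | Variance ratio | Effective d | Power, 37 v 37 | Sessions for 0.95 |
|---|---|---|---|---|
| 0 | 1.00 | 0.85 | 0.950 | 74 |
| 0.2 | 0.96 | 0.87 | 0.957 | 72 |
| 0.3 | 0.91 | 0.89 | 0.966 | 68 |
| 0.5 | 0.75 | 0.98 | 0.986 | 56 |

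**4. Gain if a subject intercept is shared across a participant's two sessions.** Set total variance to 1 and the between-session correlation to ICC. After adjustment, the session variance is v = 1 − r² and the covariance is c = ICC − r². Let p be the share of participants with the same state in both sessions, with CC and DC balanced. The variance of the CC-DC effect is proportional to

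1 / [p/(v + c) + (1 − p)/(v − c)].

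Assume ICC = 0.5 and r = 0.5. Without the covariate, v + c = 1.5 and v − c = 0.5. With it, v = 0.75 and c = 0.25, so v + c = 1.0 and v − c = 0.5. The ratio, with to without, is [p/1.5 + (1 − p)/0.5] / [p/1.0 + (1 − p)/0.5]:

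- p = 1: 0.667 / 1.000 = 0.67
- p = 0.8: 0.933 / 1.200 = 0.78
- p = 0.5: 1.333 / 1.500 = 0.89
- p = 0: 2.000 / 2.000 = 1.00

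The covariate leaves v − c unchanged, so participants who switch state gain nothing from it. The article does not give p.

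**5. Which reading applies?** Taken literally, subjects nested within sessions do not link a participant's two sessions, which is close to step 3. If a shared subject intercept is meant, step 4 applies.

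**6. The interaction.** Whether sound processing differs between CC and DC is the condition-by-stimulus term, a difference taken within a session. If one awake value A per participant enters as bA, it contributes bA to both stimulus levels, and bA − bA = 0. It cannot sharpen that term. A stimulus-matched awake value leaves b(A₁ − A₀) in the difference, and a covariate-by-stimulus term also leaves a non-zero contribution. Either form can help.

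**The case against.** The strongest reply is that no statement in the plan is wrong. Covariate adjustment is optional, the article is a condensed account, and the full protocol or analysis plan may use the awake run. This stands in part. The finding is limited to the article, but the article does write out the group model with named adjustment terms and gives no reason for leaving this one out.

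The benefit is also uncertain. Propofol may weaken r, and at r = 0.2 the variance gain is 4% even with independent sessions. Participants who change state already serve as their own controls under a shared intercept. At the planned d the power is already 0.950. All of this stands and limits the size of the point. On the other side, section 2.8 says that no fMRI effect size was available, so 0.85 is borrowed from EEG data, and section 2.9.2 corrects for the number of ROIs.

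The Introduction criticises contrasting disconnection with wakefulness. That concerns wakefulness as a comparator. A participant-level covariate leaves the CC-DC contrast as it is.

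A reader might infer three stronger claims that the documents do not support:

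- That the study is underpowered or its sample size wrong: the 74 sessions reproduce.
- That the full r-squared gain is assured: it applies to the total variance of independent sessions, and shrinks with a shared intercept as more participants switch.
- That most of the contrast is between people: the article gives no frequency for single-session or same-state participants.

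**Conclusion.** The point holds as an efficiency and confounding improvement. The article schedules a measurement of the same outcome before the non-randomised state arises and uses it in none of its analyses.

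The gain ranges from nothing to moderate. With independent sessions the variance falls by 4% to 25% for r between 0.2 and 0.5. With a shared subject intercept, at ICC 0.5 and r = 0.5, it falls by 33% if all participants keep one state, by 11% if half do, and not at all if all switch. The values of r, ICC and the same-state share are assumptions. The reduction in confounding cannot be quantified from the article, and it covers only those stable differences that the awake response reflects. That the run is unused in the article is certain; how much would be gained is not.

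**What to change.** In section 2.9.5, prespecify each participant's awake value of the same outcome as a fixed-effect covariate: the same ROI for Hypotheses 1-3, the same ROI pair for Hypotheses 4-5, and the awake spectral measure for Hypothesis 7. Where the model contains stimulus or block type, enter the awake value matched to that type, or add a covariate-by-stimulus term, so that it also serves the condition-by-stimulus interaction. State in the same place whether the subject effect is shared across a participant's two sessions, since the gain depends on it. If the awake run is meant for another purpose, say so and give the reason for leaving it out of these models.

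The cost is a sentence or two of text and one or two degrees of freedom per model. No new data and no change to the sample size are needed.

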**Figure 2 fig2:**
[figure not shown]
Schematic representation of the experimental design. Green arrows indicate loss of responsiveness; red arrows, regain of responsiveness; sound symbol, auditory oddball stimulation; alarm clock, awakening attempt; speech bubble, collection of subjective reports. fMRI acquisitions will be conducted throughout LOR1 and LOR2 and concluded prior to the initiation of the awakening attempt. Created with BioRender.com.

From the beginning of the sedation, to monitor responsiveness, participants will be instructed to perform a continuous task of alternately pressing the left and right keys of a box-shaped keypad. Propofol will be infused until loss of volitional motor activity which will be used as a proxy for loss of responsiveness (LOR). LOR will be defined as three consecutive minutes in which the participant has stopped pressing keys and neither speaks nor moves spontaneously. Propofol will be administered by a computer-controlled continuous infusion (target-controlled infusion—TCI) using a pharmacokinetic model to achieve stable plasma and effect-site propofol concentration (Schnider et al., 1999). The initial target for induction will be set at 1 μg.ml^−1^, and progressively increased (waiting five minutes between each increase in concentration) until LOR as follows: from the initial target, propofol concentration will be increased by a step of 0.5 μg.ml^−1^ to 1.5 μg.ml^−1^; if LOR will not be reached at 1.5 μg.ml^−1^, propofol will be increased by a step of 0.2 μg.ml^−1^ until 1.9 μg.ml^−1^. If LOR will not be reached at 1.9 μg.ml^−1^ propofol will be increased by steps of 0.1 μg.ml^−1^ until LOR. This will ensure to determine, for each subject, the precise concentration at which LOR occurs. This approach minimizes the risk to exceed the dose required to reach LOR. The higher the dose, the more difficult the recovery of responsiveness may become. Since the aim is to target LOR and not loss of consciousness, the maximum propofol concentration will be set at 4 μg.ml^−1^. This sedative dosage will also allow the participants to remain in spontaneous ventilation. When participants lose responsiveness, we will wait 5 min for the drug to stabilize, and then we will begin the training session. The goal of the training session is to fine-tune the propofol concentration to maximize the chances of having both LOR and intelligible reports upon regain of responsiveness (ROR) at the same propofol concentration. During the training session (outside the MRI scanner bore, but on the MRI table), we will attempt to awaken participants by performing an arousal protocol that will consist of (1) calling the volunteer aloud through the MRI microphone for up to 2 times, (2) if unsuccessful, lightly shaking volunteer’s shoulders for up to 2 times, (3) if unsuccessful, applying moderate painful stimulation, i.e., pinching the skin of the forearm for up to 2 times. If, after three runs of the protocol, participants are still not responsive, we will decrease the propofol concentration by 0.1 μg.ml^−1^, wait five minutes and repeat the arousal protocol a second time. This process is repeated until participants are able to recover responsiveness. Once responsiveness has been recovered, participants will be asked questions (see “interviews following ROR”) to verify their state of (dis)connectedness and (un)consciousness. If participants are unable to speak intelligibly, the concentration of propofol will be reduced by steps of 0.1 μg.ml^−1^ (always waiting 5 min between steps) until reports become intelligible. Once the right concentration has been identified, we will wait for participants to spontaneously lose responsiveness again, and we will end the training session with participants unresponsive (i.e., LOR1).

LOR1 will mark the beginning of the experimental session. After LOR1, we will acquire 10 min of resting-state (RS) fMRI followed by 15 min of task-based fMRI, i.e., passive listening to a sequence of oddball auditory stimuli. After concluding the fMRI acquisition and without altering the drug concentration, we will attempt to awake participants by performing the arousal protocol described above. If the participant does not regain responsiveness after one execution, the protocol will be repeated a maximum of two times. If the participant does not regain responsiveness after three executions, the participant will be defined unarousable. In case of ROR, participants will be questioned about their experience during the period of unresponsiveness to determine whether they were (un)conscious and (dis)connected (see “interviews following ROR”). After the first ROR (ROR1), we will wait a maximum of 10 min for the participant to spontaneously lose responsiveness a second time (LOR2). If the participant does not lose responsiveness in the 10 min following ROR1, we will increase the propofol concentration up to three times in 0.1 μg.ml^−1^ increments. If, after increasing the concentration, the participant does not reach LOR2, the LOR attempt will be considered unsuccessful, and the experiment will be terminated. In the case that LOR2 succeeds, the procedure described above for ROR1 will be repeated for ROR2. Finally, the end of the experiment is marked by termination of the drug infusion. This protocol has been fine-tuned based on previous work of our team (Bonhomme et al., 2016).

### Interviews following ROR

2.3

After every successful ROR, participants will be subjected to the following 6-question interview (and provided with the following possible answers):

Did you have any sensations or thoughts before you were awakened? Yes/No/Not sure/NothingDid you hear the tones? Yes/No/Not sureDo you think you were awake, having a dream or unconscious? Awake/Dream/Unconscious/Not sureDid you hear one or two different tones? One/Two/Not sure/NothingWas this experience more centered on yourself or on the environment? Myself/Environment/NothingDid you rather think, or did you see many things? Think/See/Not sure/Nothing

The first and third questions will verify that participants were (un)conscious during the period of unresponsiveness and the second question will verify the (dis)connectedness of participants during the period of unresponsiveness. The last three questions will serve two purposes: to gather more detailed information on the experience during the period of unresponsiveness and to check the consistency of the reports. Probing the presence of the experience/perception of sounds will strengthen the reliability of the answers to the first two questions (e.g., the participant might answer that he/she did not hear any sounds, but then answer the question “did you hear one or two tones?” with “two”). This interview will identify four different states: (1) awakening without any recall of experiences; (2) connected dreaming; (3) disconnected dreaming and (4) wakefulness. State 1 will be discarded as it cannot be classified in either of the two categories of interest in this study. Connected consciousness (i.e., connected dreaming) will be considered to have occurred during the unresponsive period if participants answered “Yes” to questions number 1–2 and disconnected consciousness if participants replied “Yes” to question 1 and “No” to question 2. In the case of conflicting answers, we will consider participants to have been connected conscious if they provide a positive response to at least one question amongst numbers 1,5,6 or if they respond with “having a dream” to question number 3, in addition to a positive response to at least one question amongst numbers 2 and 4. Participants responding with “awake” to question number 3 will be excluded, as they will be considered not to be in a state of connected consciousness during a dream-like state but rather awake. If participants replied with “No/Nothing” to question number 2–4 and positively to at least one of the questions investigating their experience (i.e., question number 1,3,5,6) they will be considered having been disconnected conscious during the unresponsive period. Participants will be acquainted in advance with the different questions and possible answers to ensure full understanding of each question. To rule out potential arousals during fMRI acquisitions, subjects will be monitored continuously throughout the acquisition via an eye-tracking camera (EyeLink 1000plus system from SR Research, Ltd) – the eye-tracker will be used for online monitoring but not for offline analysis. In case of eye opening, MRI acquisition will be interrupted, and we will wait for participants to spontaneously fall unresponsive again. If, after 15 min, LOR does not occur, we will increase the propofol concentration up to three times in 0.1 μg.ml^−1^ increments.

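### Interview question 1 does not exclude the awakening attempt, so a session with no experience during the scan can be coded as disconnected consciousness

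*Protocol article*

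**What the plan says.** **Timing.** Section 2.2 puts the awakening attempt after the scan: "After concluding the fMRI acquisition and without altering the drug concentration, we will attempt to awake participants by performing the arousal protocol described above". The Figure 2 legend agrees.

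**Arousal protocol.** One execution (section 2.2) has three steps: "calling the volunteer aloud through the MRI microphone for up to 2 times", then light shaking of the "shoulders for up to 2 times", then "pinching the skin of the forearm for up to 2 times". On repetition: "If the participant does not regain responsiveness after one execution, the protocol will be repeated a maximum of two times". The limit is explicit: "If the participant does not regain responsiveness after three executions, the participant will be defined unarousable".

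**Interview.** After responsiveness returns, section 2.3 asks six questions. Question 1 is "Did you have any sensations or thoughts before you were awakened" and question 2 asks whether the tones were heard. Sections 2.2 and 2.3 both describe the target as the period of unresponsiveness.

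**Coding.** Yes to both questions is connected consciousness. Yes to question 1 with no to question 2 is disconnected consciousness. An awakening with no recalled experience (state 1) is discarded. On question 3, only the answer that the participant was awake leads to exclusion.

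**The concern.** Question 1 has an end point, the awakening, but no start point and no tie to the scan. A participant who has not yet responded is still unresponsive. Shakes and pinches that were felt but did not restore responsiveness therefore fall inside both the wording of question 1 and the stated target period. None of that time is imaged. Question 2 concerns the tones, which were played only during the scan, so the two answers that define the label need not refer to the same time.

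The error runs one way. Someone with no experience during the scan did not hear the tones, so a mislabelled session of this kind enters the disconnected group and not the connected one. That group could then mix disconnected experience with absence of experience. The Introduction criticises earlier anaesthesia studies for this conflation, and the Discussion says that both groups are in a dream-like state. The connected-versus-disconnected comparison of the BOLD data rests on this label.

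**Working it through.** **1. Number of arousal stimuli (inputs from section 2.2)**

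| Input | Value |
|---|---|
| Calls per execution | up to 2 |
| Shakes per execution | up to 2 |
| Pinches per execution | up to 2 |
| Executions | 1 + 2 repeats = 3, matching the plan's own limit of three |

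Stimuli per execution: 2 + 2 + 2 = 6. Maximum per awakening: 3 × 6 = 18. If the k-th stimulus restores responsiveness, k − 1 came earlier, all unscanned. The range is 1 − 1 = 0 (first call works) to 18 − 1 = 17 (last pinch of the third execution works).

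**2. Coding path.** Take a participant who recalls nothing from the scan but felt one failed shake or pinch.

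| Question | Truthful answer | Effect under section 2.3 |
|---|---|---|
| 1, sensations or thoughts | Yes | counts as experience |
| 2, heard the tones | No | with question 1, gives disconnected |
| 3, awake, dream or unconscious | Unconscious or not sure | no exclusion |
| 4, one or two tones | Nothing | no evidence of hearing |
| 5, self or environment | any of 3 options | does not reverse the label |
| 6, think or see | Nothing | does not reverse the label |

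The 2 answers to question 3 and 3 answers to question 5 give 2 × 3 = 6 patterns. All six are coded disconnected through the main rule. Had the participant answered no to question 1 and nothing to question 5, the session would not have been classified.

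**3. Whether the model repairs it.** Section 2.9.5 enters time to ROR as a fixed effect alongside condition. This adjusts the mean of the outcome. Condition is still entered as coded, so a wrong label stays wrong.

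**4. Illustration only.** The documents give no rate of mislabelling. The plan's governing sample size is 74 sessions (d = 0.85, ratio 1, two-sided α 0.05, power 0.95), and a noncentral t calculation with 37 against 37 reproduces it. Assume that a share m of sessions coded disconnected carries no difference from the connected group, with the standard deviation unchanged. Then d′ = 0.85 × (1 − m).

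| Assumed m | d′ | Power, 37 vs 37 |
|---|---|---|
| 0 | 0.85 | 0.95 |
| 0.10 | 0.765 | 0.90 |
| 0.20 | 0.68 | 0.82 |
| 0.30 | 0.595 | 0.71 |

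This shows one direction. If sessions without experience show even weaker stimulus processing than truly disconnected ones, the contrast would be enlarged and attributed to the wrong cause.

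**The case against.** The best defence is that question 1 is aimed at the right period. Sections 2.2 and 2.3 refer it to the whole time of unresponsiveness, which includes the scanned task, and section 2.2 uses awakening for the act of performing the arousal protocol. Many participants may therefore take the question to mean before anyone tried to wake them. This stands against a stronger reading, that question 1 covers only the arousal attempt. The text does not support that reading: the window is open and includes the attempt, but is not confined to it. The ambiguity remains, because nothing tells the participant where to stop, and the Discussion describes such reports as concerning the moment just before responsiveness returns.

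Second, training tunes the concentration so that participants can be roused and speak intelligibly, which makes the count of 17 unlikely. That also stands, and 17 should be read only as a ceiling. But training lowers the concentration for failed arousal only after three unsuccessful runs, so it does not make arousal at the first call the expected outcome.

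Third, participants learn the questions in advance and go through the same arousal and interview in training, and someone who noticed being shaken may say they were awake and be excluded. These help in part. The article does not say that the briefing excludes the awakening attempt; a full interview script may, but it is not shown.

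Fourth, a reader might see a second route through question 5, where *environment* counts as a positive answer even when question 1 is no. That depends on the fallback rule, which asks for no or nothing on questions 2–4 although question 3 offers neither. The route is unclear, and the point does not need it.

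**Conclusion.** The point holds as a gap in the wording of question 1 and in the coding rule. A session with no experience during the scan can be labelled disconnected consciousness when it should be discarded, and no stated check removes it. The path needs at least one failed arousal stimulus that is felt and later reported, so it cannot arise when the first call succeeds.

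The size is unknown. A reader might infer that a definite share of the disconnected group is contaminated, but the documents give neither the rate of awakenings without recall nor how often arousal stimuli are reported as experience. They also do not fix the split between the groups, so any such share would rest on assumed rates. The power figures above are conditional on an assumed m and on equal groups. The case for acting is that the label carries the main comparison, the change is small, and labels collected without it cannot be reliably corrected afterwards.

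**What to change.** - Add *before we began calling or touching you* to question 1. Keep the question open and do not mention the sounds in it, since naming them first could cue the answers to questions 1 and 2.
- In the advance briefing, explain that questions 1, 3, 5 and 6 exclude the awakening attempt.
- Record the execution (first, second or third) and the step (voice, shake or pinch) at which responsiveness returned.
- Repeat the connected-versus-disconnected contrast in sessions roused by voice at the first execution. With up to 2 calls in that step, these sessions have at most 2 − 1 = 1 earlier stimulus and no earlier touch.

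Cost: a slightly longer question for a sedated participant, one extra recorded item and one sensitivity analysis on a smaller sample. That subset also selects the more easily roused participants, so a different result there would not by itself prove mislabelling. No dose, arousal step or other clinical rule changes.
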